**Methods:**

Observational pilot studies are ongoing in Burkina Faso, Mozambique, Nigeria, and Rwanda, leveraging dual-AI ITN rollouts nested within the 2019 and 2020 mass distribution campaigns in each country. Enhanced surveillance occurring in select study districts include annual cross-sectional surveys during peak transmission seasons, monthly entomological surveillance, passive case detection using routine health facility surveillance systems, and studies on human behaviour and ITN use patterns. Data will compare changes in malaria transmission and disease burden in districts receiving dual-AI ITNs to similar districts receiving standard pyrethroid-only ITNs over three years. The costs of net distribution will be calculated using the provider perspective including financial and economic costs, and a cost-effectiveness analysis will assess incremental cost-effectiveness ratios for Interceptor® G2, Royal Guard®, and piperonyl butoxide ITNs in comparison to standard pyrethroid-only ITNs, based on incidence rate ratios calculated from routine data.

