#### Epidemiological surveillance analysis

The trials are planned under a superiority, difference-in-differences (DiD) framework. The comparisons will consist of one-sided tests of the null hypothesis that the outcomes (reductions in parasite prevalence or case incidence rate from baseline to end line) in each intervention district are statistically the same as the outcomes in the appropriate control district control arm.

Malaria infection prevalence, determined by RDT tests during the cross-sectional surveys, will be analysed by an appropriate difference-in-differences model comparing changes in prevalence from year to year across study districts (intervention type). Considering sample size constraints, a single indicator age group will be targeted using a clustered sampling approach, clustering observations at a sub-district level (either by sector, health facility catchment, or village—whichever is most practical). Statistical analysis is done using Stata (version 14.2 or later). A difference-in-differences approach will assess matched-pair comparisons of the mean change in malaria prevalence from year to year, before and after ITN distribution across each study districts (intervention/control) comparison. The approach taken within each evaluation setting is powered independently to compare changes in prevalence observed in the ITN intervention districts to changes in the prevalence observed in the appropriate ITN control district. However, given the proposed study design and sampling frame, secondary post-hoc analyses, with Bonferroni’s correction for multiple comparisons, will likely be able to detect an effect size difference of around 20% between any two ITN types at 24 months. The protective efficacy of dual-AI ITNs is determined by multilevel logistic regression model for each year, adjusted for age and individual ITN use the previous night, with clustering at the district level.

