For passive case detection (PCD), an observational time-series study design using malaria surveillance data from the district health system will be used to compare trends in malaria case incidence in all age groups using a difference in differences approach. Monthly crude case incidence rates will be calculated at the health facility level by dividing the number of all positive malaria tests (RDT and blood smear) obtained that month by the estimate health facility catchment area population. Appropriate multivariate regression models accounting for the clustering of health facilities by district and for possible confounding factors (e.g., a negative binomial regression analysis of monthly case incidence rates likely to include rainfall amount and health facility catchment area population size), will also be utilized to estimate incidence rate ratios and incremental protective efficacy for IG2, PBO and RG ITNs. Alternatively, test positivity rates (the number of negative and positive test results obtained from suspected cases at the health facility level, stratified by study arm) may also be used to obtain odds ratio estimates from an appropriate logistic regression model. Raw datasets will be cleaned and transformed using Microsoft Excel (Microsoft Corp., Redmond WA) and Tableau v10 (Tableau Software Inc., Seattle WA) and all formal statistical analyses will be done using Stata v14 (StataCorp LLC, College Station TX).

ITN ownership, use, and coverage estimates will be calculated using standard methods recommended by the Surveillance, Monitoring and Evaluation Working Group of the RBM Partnership to end Malaria (https://endmalaria.org/node/990/related-material).

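### The example incidence model puts a negative binomial on rates rather than counts with a population offset, so its model-based standard error would depend on the rate unit

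*Protocol article*

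**What the plan says.** All of this is in the protocol article. Under Epidemiological surveillance analysis, the passive case detection paragraph obtains the monthly crude rate at each facility by "dividing the number of all positive malaria tests (RDT and blood smear) obtained that month by the estimate health facility catchment area population". No multiplier is given, so read literally the rate is per person.

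The next sentence turns to regression models "accounting for the clustering of health facilities by district and for possible confounding factors". The example it offers is "a negative binomial regression analysis of monthly case incidence rates likely to include rainfall amount and health facility catchment area population size". Such models "will also be utilized to estimate incidence rate ratios and incremental protective efficacy for IG2, PBO and RG ITNs". A logistic model of test positivity is offered as an alternative. The paragraph mentions no count outcome, no offset or exposure term and no variance estimator.

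The same section plans "one-sided tests of the null hypothesis" for both prevalence and case incidence. In the Abstract (Methods), the incremental cost-effectiveness ratios are "based on incidence rate ratios calculated from routine data". Study objectives also ties cost-effectiveness to the case incidence results.

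**The concern.** The negative binomial variance is μ + kμ², where μ is the mean and k the dispersion. The first term is the Poisson variance of a count. Multiplying the outcome by a constant c multiplies a true variance by c², but the term μ grows only by c. If the outcome is a rate, the assumed relation between mean and variance therefore changes with the unit (per person, per 100, per 1,000), although the data are the same. The likelihood also gives a small and a large catchment the same variance at equal rates.

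At stake are the confidence intervals and one-sided tests for the rate ratios from routine data. Too small a unit inflates the standard error and could hide a real benefit. Settings analysed in different units would not have comparable precision.

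**Working it through.** **Plan's own figure.** The article states no sample size, power or standard error for the incidence model, so there is nothing to reproduce.

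**Assumed inputs (not in the documents).** Two districts with 15 facilities each; 36 months, 12 before and 24 after the campaign; median catchment 8,000; true rate ratio 0.7. Three scenarios, 12 data sets each:
- A: 30 cases per 1,000 per month, k = 0.3, between-facility SD 0.4.
- B: 5 per 1,000, k = 0.3, SD 0.4.
- C: 5 per 1,000, k = 0.05, SD 0.2.

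Only the 12-month baseline is anchored in the article, which starts the routine series about a year before the campaigns.

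**Models compared.** Both are maximum-likelihood negative binomial fits with district, period, district-by-period and rainfall terms: (a) the rate times a unit u as outcome, with population as a covariate; (b) the count as outcome, with log(population) as offset.

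**Median model-based standard error of the log rate ratio**

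| Outcome | A | B | C |
|---|---|---|---|
| Count with offset | 0.085 | 0.089 | 0.044 |
| Rate per person | 0.70 | 1.73 | 1.80 |
| Rate per 10 | 0.22 | 0.55 | 0.57 |
| Rate per 100 | 0.087 | 0.17 | 0.18 |
| Rate per 1,000 | 0.084 | 0.087 | 0.058 |
| Rate per 10,000 | 0.085 | 0.089 | 0.043 |

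The per-person ratios to the offset model are 0.704/0.0848 = 8.3, 1.73/0.0888 = 19.5 and 1.80/0.0436 = 41. Per 100 the ratios are 0.167/0.0888 = 1.9 in B and 0.182/0.0436 = 4.2 in C. Per 1,000 in C the ratio is 0.0576/0.0436 = 1.32.

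At the units where the dispersion estimate fell to zero, 2 to 7 of the 12 fits gave no model-based standard error and are left out of the medians.

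**Hand check, scenario A.** When the dispersion estimate reaches zero, the standard error is the Poisson one for the rate itself, √Σ(1/expected cell total).
- The per-person cell totals are 15 × 12 × 0.03 = 5.4 (before, each district), 15 × 24 × 0.03 = 10.8 (after, control) and 10.8 × 0.7 = 7.56 (after, intervention).
- √(2/5.4 + 1/10.8 + 1/7.56) = √0.595 = 0.77, near the simulated 0.70.
- At one sixth of the incidence, 0.77 × √6 = 1.89, near 1.73 and 1.80.
- For the offset model, the mean count is 8,000 × 0.03 = 240 and the fitted k is 0.426 (it absorbs facility variation). √[(0.426 + 1/240)(2/180 + 2/360)] = √0.00717 = 0.085, as simulated.

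**Where the unit stops mattering.** The rate model can match the true relative variance only if 1/(u × rate) is smaller than that variance, because k cannot go below zero. The break points are:
- A: 1/(0.430 × 0.03) ≈ 78.
- B: relative variance 0.439 + 1/40 = 0.464, so 1/(0.464 × 0.005) ≈ 431.
- C: 0.082 + 1/40 = 0.107, so 1/(0.107 × 0.005) ≈ 1,870.

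This explains why per 100 is adequate in A but not in B, and why per 1,000 is not adequate in C.

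**Effect on an interval.** For a rate ratio of 0.7 in A, 0.7 × exp(±1.96 × 0.085) gives 0.59 to 0.83, and per person 0.7 × exp(±1.96 × 0.70) gives 0.18 to 2.76. In B per 100, exp(±1.96 × 0.17) gives 0.50 to 0.98, against 0.59 to 0.83 with the offset.

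**What does not change.** In A the median rate ratio was 0.716 to 0.727 across units, against 0.718 with the offset. Facility-clustered sandwich standard errors were 0.074–0.078, 0.074–0.076 and 0.033–0.034 across units in A, B and C. With counts and an offset, one data set gave 0.0810 whether population was in persons, thousands or hundreds of thousands.

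**Other assumed inputs.** A simulation with 20 facilities per district, 20 cases per 1,000 per month and rate ratio 0.80 gave 0.055 with the offset, 0.078 per 100 and 0.775 per person. A third gave 0.081 with the offset against 0.91 per person at 20 per 1,000, and 0.083 against 1.84 at 5 per 1,000; its error at per 1,000 was at most about 14%.

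**The case against.** A reader might infer that the plan commits to a faulty model and that its intervals will be invalid. The article does not support that. The model is offered as an example, with covariates described only as likely, and the text does not rule out an exposure term. A negative binomial regression yielding incidence rate ratios may be shorthand for counts with a population exposure. The Discussion refers to a common analysis framework and a main analysis plan, neither shown, where such detail usually sits. This stands as a limit on the claim. Against it, this is the only incidence regression the article names, and it gives the outcome as a rate and population the role of a confounder.

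A second objection is that the required allowance for clustering removes the problem. With facility-clustered robust standard errors it nearly does. But no estimator is named, and the level mentioned is the district. Table 1 has three or four districts per evaluation and so two per comparison, too few for a dependable district-clustered sandwich.

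Third, a reader might infer that the rate ratios, and so the mean cost per case averted, would be biased. They would not, to any extent seen here. The inflation is also conservative for a superiority claim, failed fits at very small units would be noticed, and incidence is not the outcome on which the evaluations are powered. All of this stands.

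Finally, population serving as both divisor and covariate is not in itself an error. Log population beside a rate merely frees the coefficient that an offset fixes at 1, and catchment size may be a genuine confounder.

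**Conclusion.** The concern holds as a correction to the wording of the example model. Followed literally, it gives a model-based standard error that depends on a unit the article never states. Under the assumed inputs, the excess is about 8 to 41 times per person and about 2 to 4 times per 100 at 5 cases per 1,000 per month. It is between nothing and about 32% at per 1,000, and about 1% or less at per 10,000. Low incidence and low overdispersion make it worse.

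The consequence is confined to model-based standard errors, intervals and tests. Rate ratio estimates are nearly unchanged and facility-clustered robust standard errors nearly unaffected. The facility numbers, incidence, dispersion and catchment sizes are all assumptions, so only the direction and rough range should be relied on.

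**What to change.** Replace the example model with the following: monthly facility counts of positive tests, analysed by negative binomial regression with log(catchment population) as offset (coefficient fixed at 1) and the district-by-period difference-in-differences term. Name standard errors that allow for repeated months within a facility, for instance by clustering on facility. Rainfall can stay. Population size may stay as a covariate only if it is justified as a confounder in addition to the offset. The crude rates can still be reported descriptively, with their unit stated.

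The cost is a sentence or two of analysis wording; data and software are unchanged.

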#### Entomological surveillance analysis

Vector species–specific entomological data are analysed by comparing changes in monthly vector density trends across districts using a zero-adjusted negative binomial regression model. Species-specific biting behaviours, entomological inoculation rates, and insecticide resistance patterns are compared again using appropriate t-tests or similar methods.

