## Study objectives

The overall aim of the study is to describe the effectiveness and cost-effectiveness of IG2, RG, and PBO ITNs in comparison to standard pyrethroid-only ITNs. Specific objectives are organized into five study components: (1) malaria epidemiological surveillance to evaluate the impact of dual-AI ITNson malaria burden, (2) entomological surveillance to evaluate the impact of dual-AI ITNs on key entomological outcomes (3) anthropological data to assess how transmission risk is influenced by human behaviours, (4) assessment of the chemical and physical durability of the new ITN types, and (5) evaluation of the cost and cost-effectiveness of dual-AI ITNs.The epidemiological objective is to evaluate the effectiveness of IG2, RG, and PBO ITN distributions, compared to standard pyrethroid-only ITN mass distributions, in reducing:Malaria prevalence measured during annual cross-sectional surveys in children 6 months to 5 years (Burkina Faso, Mozambique, and Nigeria) and all ages (Rwanda).Passive malaria case incidence rates measured using routine surveillance systems (DHIS2).The entomological objective is to compare post-ITN distribution trends in vector densities, human biting rates, and entomological inoculation rates using CDCLTs and HLCs and to establish baseline. In addition, entomological objective is to evaluate insecticide susceptibility patterns in the primary vector species populations.The anthropological objective is to assess how human behaviour influences exposure risk and understand the key drivers of ITN use and non-use behaviour across districts with different types of ITN types.The ITN durability monitoring objective is to assess the attrition, survivorship, physical integrity, and insecticidal bioefficacy of all ITN types at baseline, 12 months, and 24 months.The cost-effectiveness objective is to combine data on product effectiveness (based upon case incidence rates measured for objective 1) and data on product prices and costs of delivery and deployment to estimate a mean cost per case averted for each ITN type.

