### Entomological component

A core set of collection methods are undertaken for the entomological surveillance component of the study, including human-baited US Centers for Disease Control and Prevention light traps (CDCLTs), human landing collections (HLCs), and larval sampling, supplemented by pyrethrum spray catches in Nigeria where HLCs are not performed (Table 4). Entomological investigations are nested within routine NMCP vector surveillance programme activities as much as possible so that within each district, operational sentinel villages with existing entomological surveillance capacity are enhanced to support (1) increased sampling from additional houses and (2) molecular characterization of vector species collected. In each county, pre-existing entomological sentinel sites had been established on the basis of historical mosquito densities, ease of access, and safety. They do not necessarily overlap with the same communities participating in the household surveys, which are selected randomly.

**Table 4 Tab4:** Entomological methods by country

		Burkina Faso	Northern and Western Mozambique	Nigeria	Rwanda
CDCLT collections	Number of collections per district	• 3 villages with 6 houses each		• 4 villages with 2 houses per village • Paired indoor-outdoor collections	• 9 villages with 5 houses per village
	Frequency	• Once per week • Two consecutive nights		• Three consecutive nights • Once a month	• Two consecutive nights • Twice per month
HLCs	Number of collections per district	• 3 villages with 2 houses each • Paired indoor-outdoor collections	• 3 villages with 3 houses each • Paired indoor-outdoor collections		• 3 houses per village • Paired indoor-outdoor collections
	Frequency	• Concurrent with CDCLT collections (different houses)	• Two consecutive nights • Every other month for 24 months		• Concurrent with CDCLT collections (different houses)
Pyrethrum spray catches	Number of collections per district			• 48 houses	
	Frequency			• Once monthly	
Larval sampling	Frequency	• Surveys at least once per year	• Surveys at least once per year (aligned with standard NMCP surveillance)	• Surveys at least once per year	• Surveys at least once per year

*CDCLT* US Centers for Disease Control and Prevention light trap, *HLC* human landing collection, *LGA* local government area

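### Biting and inoculation rates are to be compared between districts by t-tests with no stated allowance for village, although the data are repeated collections in a few fixed sentinel villages

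*Protocol article*

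**What the plan says.** Under Study objectives, the entomological aim is to "compare post-ITN distribution trends in vector densities, human biting rates, and entomological inoculation rates". The section Entomological surveillance analysis then splits the outcomes. Vector density is analysed by "comparing changes in monthly vector density trends across districts using a zero-adjusted negative binomial regression model". For the rest, with biting behaviours heading the same sentence, "entomological inoculation rates, and insecticide resistance patterns are compared again using appropriate t-tests or similar methods". Neither sentence mentions village, house or repeated nights.

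The section Entomological component and its Table 4 describe the sampling. The "pre-existing entomological sentinel sites had been established on the basis of historical mosquito densities, ease of access, and safety", so the villages are fixed and not randomly drawn. Per district there are "3 villages with 6 houses each" for light traps in Burkina Faso, "3 villages with 3 houses each" for human landing collections in Mozambique, "4 villages with 2 houses per village" for light traps in Nigeria, and 9 villages of 5 houses for light traps in Rwanda. Collections run on consecutive nights and recur; in Mozambique, in alternate months over 24 months.

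The section Entomological sampling says that no statistical criteria were set beforehand and that variability and power will be described afterwards. By contrast, Epidemiological surveillance analysis names clustering for both prevalence and facility-based incidence.

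**The concern.** Mosquito collections from one village share breeding sites, housing and location, so they resemble each other more than collections from another village. A two-sample t-test on individual house-nights, or on village-months, counts each as fresh evidence about the district. With 3 or 4 villages per district, one village near a productive breeding site could then move a district mean enough to look like a net effect, with an interval that is too narrow.

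A second mismatch is that the objective concerns trends after distribution, while a plain t-test compares levels. Only the density outcome is given a trend model.

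The entomological results are not the powered outcome, but the Discussion relies on them to explain differences in cost-effectiveness and presents the inoculation-rate results as important evidence. Falsely precise entomological comparisons could be read as confirming or contradicting an epidemiological finding.

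**Working it through.** The protocol gives no entomological sample size, power or alpha, so there is no figure of its own to reproduce.

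**Inputs from Table 4.** Villages per district, houses per village, nights per round and, for Mozambique, the number of rounds (24 months at every other month = 12).

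**Assumptions.** Two-sided 5% test; village ICC of 0.01, 0.05 or 0.10; 24 months of collection in Nigeria, Rwanda and Burkina Faso; one two-night session a month in Burkina Faso, which is sparser than the weekly frequency in Table 4.

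**Formulae.** With m house-nights per village, design effect D = 1 + (m − 1) × ICC. The actual error of a nominal 5% test that treats house-nights as independent is 2 × [1 − Φ(1.96/√D)].

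**Worked case: Mozambique human landing collections, one location (indoor or outdoor).**
- m = 3 houses × 2 nights × 12 rounds = 72.
- At ICC 0.05, D = 1 + 71 × 0.05 = 4.55.
- 1.96/√4.55 = 0.919, so the error is about 36%.

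| Series | Villages per district | m | ICC 0.01 | ICC 0.05 | ICC 0.10 |
|---|---|---|---|---|---|
| Mozambique landing collections | 3 | 72 | 13% | 36% | 49% |
| Nigeria indoor light traps | 4 | 2 × 3 × 24 = 144 | 21% | 49% | 62% |
| Burkina Faso light traps | 3 | 6 × 2 × 24 = 288 | 32% | 62% | 72% |
| Rwanda light traps | 9 | 5 × 2 × 2 × 24 = 480 | 42% | 70% | 78% |
| One Mozambique round only | 3 | 3 × 2 = 6 | 6% | 8% | 11% |

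At ICC 0 the error is 5%. Simulation of two districts with no net effect and a normal outcome (2,000 runs per case) agreed within about 3 percentage points. Skewed negative binomial counts (assumed mean 3, dispersion 1) gave 38%, 49% and 68% for Mozambique, Nigeria and Rwanda at ICC 0.05.

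**Village-month means as the unit.** In Mozambique each is a mean of 6 house-nights. At a house-night ICC of 0.05, the ICC of these means is 0.05/(0.05 + 0.95/6) = 0.24. With 12 per village, D = 1 + 11 × 0.24 = 3.64, 1.96/√3.64 = 1.03, and the error is about 30%; simulation gave about 32%. Averaging to village-months therefore does not cure the problem.

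**Village means as the unit.** Simulated error was about 4% to 6% in every case. Degrees of freedom are 2 × villages − 2: 4 with 3 villages (critical t 2.78), 6 with 4 villages (2.45), 16 with 9 villages (2.12).

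**Resistance.** The section Larval sampling and insecticide resistance testing combines specimens from the sentinel villages into one test population per district, annually. Village identity is lost before testing, so none of the arithmetic above applies to it.

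**The case against.** The wording allows for appropriate or similar methods and fixes no unit of analysis. A t-test on village means would satisfy it and would hold its level. A reader might infer that chance village differences will be declared net effects; the document does not support that, because it never says that house-nights are the unit. This objection stands, and the error rates are therefore conditional.

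A reader might also extend the point to resistance, or assume that the same houses are visited throughout. Neither is supported. Resistance uses pooled annual specimens, and Table 4 gives numbers and frequencies only. Reuse of sentinel houses is textually clear only for Nigeria. Reuse of sentinel villages is clear generally, and the argument needs only that.

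The calculation has limits. It uses a generic house-night outcome; inoculation rates also carry an infection component, and light-trap counts may enter mainly through the density model. If changes from before the campaign were compared, stable village differences would largely cancel; that case was not run. The Discussion, however, concedes that the baseline period was short.

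Finally, an article condenses, and the Discussion refers to a shared analysis framework that is not shown. That is a fair reason not to press for every model term. But the article does name a test here, one whose usual form assumes independence, while it names clustering for prevalence and incidence. That goes beyond missing detail.

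**Conclusion.** The point holds for biting and inoculation rates: the named test does not reflect repeated sampling in 3 to 9 fixed villages per district, and it does not address the trend objective. The plan as worded admits both an analysis with about 5% error and one with about 36% (Mozambique, ICC 0.05; 13% to 49% over ICC 0.01 to 0.10), with higher rates in the longer light-trap series. These figures rest on an assumed ICC, an assumed two-sided 5% level, assumed durations outside Mozambique, and house-nights as the unit. The density model has the same gap, since it names no village term.

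Correcting this does not make the comparison causal. Each net type has one district per evaluation, so net type and district stay inseparable, and the entomological comparison is supportive only. The change is worth making, but it does not touch the powered prevalence outcome.

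**What to change.** In Entomological surveillance analysis:

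- For biting and inoculation rates, either make the village the unit of analysis, or use a model with net type, calendar month and, where pre-campaign rounds exist, a net-type-by-period term. Include a random effect for village, a house effect where houses are reused, and village-based degrees of freedom.
- Add the same village effect to the negative binomial density model.
- Report resistance descriptively, or with between-sample variation. A village or house random effect is not suitable after pooling by district and year.
- State that intervals will be wide (4 degrees of freedom with 3 villages per district), and that the comparison is supportive and cannot separate net type from district.

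The cost is revised wording, a little more analysis of data already being collected, and wider, less favourable intervals.
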